# Vitalizing Community for Health Promotion Against Modifiable Risk Factors of Noncommunicable Diseases (V-CaN) in Rural Central India: Protocol for a Hybrid Type II Implementation Effectiveness Trial

**DOI:** 10.2196/42450

**Published:** 2023-09-29

**Keywords:** noncommunicable diseases, action research, implementation research, community-based participatory research, salutogenesis, primary prevention

## Abstract

**Background:**

Low- and middle-income countries are facing the emerging burden of chronic noncommunicable diseases (NCDs). Apart from loss of human lives and premature deaths, NCDs result in huge costs for treatment to individuals and the health system. Although NCDs develop in later life, the risk factors begin at an early age. The key to the control of the global epidemic of NCDs is primary prevention based on comprehensive community-based programs.

**Objective:**

This study aims to develop, implement, and evaluate the effect of a participatory health promotion initiative utilizing the existing mechanisms of Village Health Nutrition and Sanitation Committees (VHNSCs), women’s self-help groups (SHGs), and schools on modifiable risk factors for NCDs among young people aged 10-30 years.

**Methods:**

The proposed type II hybrid effectiveness implementation cluster randomized field trial will be conducted in the catchment area of 4 primary health centers (PHCs) in Wardha district, India, comprising 100 villages with a population of 144,000. Each PHC will be randomly allocated to one of the 3 intervention arms or the control arm. The 3-intervention arm PHCs will utilize a unique strategy with either VHNSC or SHG members or school students as change agents for health action against common modifiable NCD risk factors. This study will be implemented in 3 phases from January 2022 to December 2024. First, the preparatory phase for baseline assessments includes anthropometry, behavioral and biochemical risk factors for NCDs, and participatory development of the health promotion intervention modules. Second, the implementation phase will focus on capacity building of the change agents and implementation of the participatory health promotion initiative. The implementation will include organization of community-based events, 6-monthly participatory assessment of change, and preparation of a sustainability and exit plan toward the end of this phase. Third, the evaluation phase will consist of studying the effectiveness of each intervention strategy in the reduction of risk factor prevalence at the population level.

**Results:**

We will assess 12,000 (3000 in each arm) randomly selected individuals for behavioral risk factors and 1600 (400 in each arm) individuals for biochemical risk factors during baseline as well as endline assessments. Difference in differences, ANOVA or multivariate analysis of covariance, and regression analysis will be performed to assess the effectiveness of the interventions. Qualitative methods such as focus group discussions and stories of change will be documented and analyzed using thematic framework analysis. The implementation outcomes will be reported using the PRISM (Practical Robust Implementation and Sustainability Model) RE-AIM (Reach, Effectiveness, Adoption, Implementation, Maintenance) framework. The results are expected to be published by mid-2025.

**Conclusions:**

This study will show the magnitude of risk factors for NCDs, its determinants, feasibility, effectiveness of community-based interventions, and health promotion models for NCD prevention.

**Trial Registration:**

Clinical Trials Registration India CTRI/2020/10/028700; https://ctri.nic.in/Clinicaltrials/showallp.php?mid1=47597&EncHid=&userName=V-CaN

**International Registered Report Identifier (IRRID):**

DERR1-10.2196/42450

## Introduction

### Background

Low- and middle-income countries such as India are facing the emerging burden of chronic noncommunicable diseases (NCDs) while still struggling with the unfinished agenda of improving maternal and child health, nutrition, and infectious disease spread [1]. The burden of cardiovascular diseases, chronic respiratory diseases, diabetes, cancer, and mental disorders is predicted to increase significantly in the next 25 years [1]. NCDs are estimated to account for about 75% of all deaths in India by 2030 [1]. Cancer deaths are projected to double from 2004 to 2030, and cardiovascular disease deaths are predicted to increase from 2.7 million in 2004 to 4 million in 2030 [1]. Apart from high costs to the health system, NCDs result in high out-of-pocket expenditure. The overall economic burden of NCDs in India is estimated to amount to approximately 5%-10% of the gross domestic productivity, thus imposing huge social and economic costs, impeding not only health improvements but also economic progress and social development of the country [2]. Evidence suggests that NCDs disproportionately impact people at younger ages and are increasingly afflicting the poorer segments of the society [2,3].

The National Family Health Survey has shown that throughout India, over 10% of the population aged 15 years and older have elevated blood sugar levels and over 20% of the population have elevated blood pressure levels [4,5]. Various studies [6-9] have highlighted the need of early interventions for the primary and secondary prevention of NCD-related risk factors. For instance, a study in Central India reported that the prevalence of hypertension was 5.75% among adolescents, which highlights the need for blood pressure and nutritional monitoring among adolescents [6]. Overweight or obesity has been reported in 4.3% of schoolchildren in Wardha, with a dietary deficiency in 57% of the adolescent girls [7]. Metabolic syndrome (clustering of abdominal obesity, hypertension, disturbed glucose metabolism, and dyslipidemia) has been reported in 9.3% of the rural adult population in India [8]. A recent review from low- and middle-income countries highlights the role of community-based interventions through health-promotion initiatives in reducing the risk factors related to NCDs. Such interventions significantly reduce the risks ranging from lifestyle and diet modifications, smoking, alcohol, etc [9].

The key to the control of the global epidemic of NCDs is primary prevention based on comprehensive community-based population-wide programs. There is a common agreement that community empowerment is crucial for the success of such programs, and partnerships among different stakeholders are required to provide effective pathways for the design and delivery of NCD prevention and control programs. Although India counts on different national programs to control NCDs, the gaps in implementing these programs and a clear strategy of what works and how to implement it at the local level is lacking. Notably, health promotion is a common component in all these programs [2,9,10]. Indian states such as Tamil Nadu and Kerala have piloted efforts around NCD prevention and control through various health promotion activities [11]. Although some community-based interventions have been conducted in India, there is a great variation in terms of the components of the interventions and the target population. However, to have a population-level impact and to reach communities in the periphery, the health promotion component of the NCD programs needs to be adapted to the local context [2,9].

Few studies [12-17] focusing on lifestyle intervention programs at the community level have shown considerable benefits in terms of promoting health education through healthy diets, increasing physical activity, and screening for diabetes prevention and control [12]. A community-based study in Gujarat targeting adults for the prevention and control of diabetes, consisting of health education sessions provided by trained community health workers, led to improved knowledge of diabetes and cardiovascular diseases and a reduction in the overall blood pressure in the studied population [13]. A community-based program in India for NCD prevention and control in Ballabgarh district was evaluated by Krishnan et al [14]. Volunteers and schoolteachers were trained in addition to communication campaigns, camps, and reorientation of health services at the community level. The intervention led to better management of NCDs at health facilities [14].

Several school-based health education programs in India have successfully reduced the rates of both tobacco experimentation and offer of tobacco by peers [15,16]. School-based educational programs can significantly influence children’s behavior in inculcating healthy lifestyle practices. A school-based intervention called MARG (medical education for children or adolescents for realistic prevention of obesity and diabetes and for healthy aging) showed a significant increase in the intake of healthy foods, decrease in the intake of fried and fatty energy-dense foods, and increase in the physical activity and time spent on outdoor games along with improvements in glycemic parameters and lipid profiles [17]. The MYTRI (Mobilizing Youth for Tobacco-Related Initiatives in India; 2002-2007) project consisted of randomized controlled intervention trials that established the effectiveness of school health interventions in reducing tobacco use among Indian adolescents by reducing current tobacco use and their future intentions to use tobacco and by enhancing their health advocacy skills [16].

Several studies [18-22] have also emphasized the potential of self-help groups (SHGs) in improving health-related outcomes at the population level, especially in terms of knowledge, attitude, and practice of healthy behaviors for NCDs as well as other health-related conditions. VHNSCs were constituted under the National Rural Health Mission in India to enable community participation in health-related activities, formulate village health action plans, and implement and monitor the same in the villages. The VHNSC is responsible for the health of the villagers, and they are mandated to undertake preventive, promotive, and curative health activities at the village level [23].

In this study, we aim to develop, implement, and evaluate the effects of a participatory health promotion initiative utilizing the existing mechanisms of VHNSC, women’s SHGs, and schools on behavioral as well as biochemical modifiable risk factors for NCDs (obesity or overweight, tobacco use, stress, unhealthy diet, physical inactivity, harmful use of alcohol, high blood pressure, high blood sugar, and increased blood cholesterol) among young people in the age group of 10-30 years.

### Rationale of This Study

Randomized clinical trials have documented that lifestyle changes can prevent NCDs [24]. However, there is limited evidence, particularly in India, whether such strategies are applicable at the community level, that is, in a real-life setting. The emphasis of our proposed study is to strengthen the primary prevention of NCDs, which is often neglected under the current national health programs. Our proposed study will utilize a health promotion approach as indicated in the Ottawa Charter for Health Promotion [25] and will make efforts to empower and enable young people aged 10-30 years to exercise control and take care of their own health. Our study will focus on young people aged 10-30 years, as this age group is not covered under the National Programme for Prevention & Control of Non-Communicable Diseases (NP-NCD), and it is during this phase of life that NCD-related risk factors begin, which become habits during later years and thus become difficult to change and lead to chronic diseases. Apart from focusing on the commonly emphasized risk factors of tobacco, alcohol, and physical activity, this study will include locally feasible and acceptable strategies to reduce stress, which often is not accounted for in NCD prevention. This study will be implemented in collaboration with the district health system, utilizing the existing mechanisms of Village Health Nutrition and Sanitation Committee (VHNSC), women’s SHGs, and schools by using the principles of participatory development and therefore much more likely to be acceptable to the community and sustainable eventually. The NP-NCD currently emphasizes early diagnosis and prompt treatment and at times tends to overlook the primary prevention. Our study, which is the first of its kind in central India for health promotion against NCD risk factors among young people aged 10-30 years, will help strengthen the primary prevention component under the NP-NCD. The proposed study has the potential of producing a community-based health promotion model for the prevention of NCDs through the life cycle approach, and thus, has every chance of leading directly to improvements in population health.

## Methods

### Study Design

The proposed study will be a type II hybrid effectiveness implementation cluster randomized field trial that will be implemented in a rural area of Wardha district of Maharashtra, India, which also is a part of the field practice area of the Department of Community Medicine, Mahatma Gandhi Institute of Medical Sciences, India. This study will be performed in the catchment areas of 4 primary health centers (PHCs) of Wardha block, namely, Anji, Kharangana, Talegaon, and Waifad. As per the census of 2011, there are around 100 villages in this study area with a population of approximately 144,000 people. However, the census towns (as per census 2011) in the study area will be excluded [26]. This study will be performed from January 2022 to December 2024.

### Randomization

The proposed study will have 4 arms: 3 intervention arms and 1 control arm. The unit of randomization would be PHCs and each of the 4 PHCs will be randomly allocated using a simple randomization technique through the lottery method to 1 of the 3 intervention arms or to the control arm. The primary strategy in this study would be health promotion by creating change agents. The 3 intervention arms would differ in the source of change agents. The 3 interventions in this proposed study would be with (1) school students as change agents, (2) VHNSC members as change agents, and (3) women’s SHG members as change agents.

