##### Sample Size for Behavioral Risk Factors

We hypothesize that our interventions would reduce the modifiable behavioral risk factors for NCDs by 25% over a period of 3 years. With an assumption of the lowest prevalence of NCD-related risk factors at 13% [6-8,28,29] to detect the aforesaid difference, with 95% CIs, power of 80%, intracluster correlation coefficient of 2, an approximate sample of 12,000 participants, that is, 3000 in each arm, was calculated. Sample size was estimated using the lowest risk factor prevalence, as it gives the maximum possible sample size. We will utilize stratified random sampling (stratified by gender) to select the study participants. The sampling frame will be prepared from the already existing health and demographic surveillance system, which is established by the Department of Community Medicine, Mahatma Gandhi Institute of Medical Sciences, in 5 PHCs (including the study PHCs) covering around 113 villages and a population of about 120,000 people. The health and demographic surveillance system is updated every 6-12 months, and data from the most recent round will be used for the abovementioned purpose.

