#### Statistical Analysis Plan

The primary outcome variable for this study would be the prevalence of various modifiable NCD risk factors as compared to baseline. Descriptive analysis will be performed using proportions with 95% CIs. For the quantitative information, difference in differences analysis using *Z*-test for differences between proportions of independent samples and ANOVA or multivariate analysis of covariance will be used to find out the effectiveness of the intervention between the intervention and the control groups. Here, the 3 interventions will be evaluated independently to demonstrate the feasibility and efficacy of each of the 3 intervention modalities. In addition, multivariate regression will be performed for finding the determinants of the risk factors, and exploratory factor analysis will be performed to explain the observed variances between intervention and control groups. For the qualitative data, thematic content analysis will be performed.

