### Future Plans Based on Expected Outcomes

This study will be a value addition to strengthen the primary prevention component under the NP-NCD and Rashtriya Kishor Swasthya Karyakram, as it is going to be implemented in collaboration with the district health system, utilizing the existing mechanisms of VHNSC, community-based organizations, and frontline health workers. If proven effective, the possibility to implement the health promotion modules in the control PHC will also be explored at the end of the study. Further advocacy with the administration will be performed for scaling up of the intervention.

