### Strengths and Limitations of This Study

This cluster randomized study will provide rich evidence regarding prevention of common modifiable risk factors against NCDs. Moreover, outcome evaluation is performed in a very large sample, thereby minimizing the possibility of random errors in the results. Simple random sampling will ensure minimal selection bias. The inbuilt concept of community mobilization and preparation of an exit plan may also lead to sustenance of the program, thereby ensuring the perceived benefits to reach the people even beyond the study duration. External generalizability of this study will be limited only for rural areas with similar profiles and not for urban or tribal areas.

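### With one PHC per arm, PHC-specific change over time is aliased with the intervention, so the efficacy claim for each modality and the claim of minimal random error are not supported.

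*Protocol article*

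**What the plan says.** The Randomization section of the protocol article says "The proposed study will have 4 arms: 3 intervention arms and 1 control arm" and "The unit of randomization would be PHCs and each of the 4 PHCs will be randomly allocated using a simple randomization technique", by lottery. The Methods paragraph of the abstract agrees: "Each PHC will be randomly allocated to one of the 3 intervention arms or the control arm". The section on future plans speaks of a single control unit: "the possibility to implement the health promotion modules in the control PHC will also be explored at the end of the study". So there are four PHCs, four arms and one PHC in each.

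The Study Design section calls this a cluster randomized field trial. The Statistical Analysis Plan section names difference in differences with a Z-test for independent proportions, and ANOVA or multivariate analysis of covariance. It adds that "the 3 interventions will be evaluated independently to demonstrate the feasibility and efficacy of each of the 3 intervention modalities".

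The Strengths and Limitations section says "outcome evaluation is performed in a very large sample, thereby minimizing the possibility of random errors in the results". The only limitation it names is generalisability beyond similar rural areas.

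The behavioural sample size rests on a hypothesis that the interventions "reduce the modifiable behavioral risk factors for NCDs by 25% over a period of 3 years", starting from 13%, with 3000 people per arm.

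**The concern.** In a cluster randomised comparison, the randomised unit supplies the replication. With one PHC per arm, each intervention-control contrast has two clusters and 2 - 2 = 0 degrees of freedom for variation between PHCs. Anything that shifts the risk factors in one PHC area and not in the control area between the surveys appears in full as an intervention effect. Migration, which Table 2 lists under the external environment, is one example. Nothing in the data can show how large such shifts usually are.

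A p-value or interval computed from individuals then describes only the sampling error within these PHCs. If it is read as evidence that a modality works, its error rate is unknown and can be far above 5%. This matters because the future-plans section makes use of the modules in the control PHC depend on proof of effectiveness, and goes on to advocacy for scale-up.

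**Working it through.** **1. The plan's own figure.** Inputs from Sample Size for Behavioral Risk Factors: 13% falling by 25% to 9.75%, an absolute difference of 0.25 × 13 = 3.25 points; 80% power; two-sided 5% (assumed from the 95% CI). The usual two-proportion formula gives 1498 per arm. The stated intracluster correlation of 2 cannot be a correlation. Read as a design effect it gives 2 × 1498 = 2996, which matches 3000 per arm.

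That allowance does not cover PHC-level variation. With 3000 people in one cluster, a design effect of 2 at a single survey corresponds to a PHC-level intracluster correlation of 1/(3000 - 1) = 0.00033.

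**2. What randomisation alone can show.** Four PHCs can go to four arms in 4! = 24 ways.

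- All four PHCs: there are 4 × 3 = 12 ordered pairs of (intervention PHC, control PHC). A pair and its reverse give the same absolute difference, so the smallest two-sided p is 2/12 = 1/6. This needs a sharp null for all four arms, meaning that no PHC's outcome would differ under any allocation, because the other two arms are exchanged as well.
- One intervention PHC and the control PHC alone: there are two allocations, so the smallest p is 0.5 one-sided and 1.0 two-sided.

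Neither can reach 0.05.

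**3. Size of the error in an individual-level test.** Let tau be the SD, across PHCs, of change from baseline to endline that is not due to the intervention. The documents give no value, so a range is shown. Other assumptions: prevalence 13%, 3000 per arm per round, independent samples at the two rounds, within-PHC design effect 2 (effective n = 1500), and a test that uses the correct within-PHC standard error.

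- Within-PHC SE of the difference in differences: sqrt(4 × 0.13 × 0.87 / 1500) = 1.74 points.
- True SD of the estimate under no effect: sqrt(1.74² + 2 tau²).
- False-positive rate: 2 × [1 - Phi(1.96 × 1.74 / sqrt(1.74² + 2 tau²))].

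| tau (points) | True SD (points) | False-positive rate |
|---|---|---|
| 0 | 1.74 | 5% |
| 0.25 | 1.77 | 5.5% |
| 0.5 | 1.88 | 6.9% |
| 1 | 2.24 | 12.9% |
| 2 | 3.32 | 30.5% |

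**4. Whether a larger sample helps.** The term 2 tau² does not contain n. Doubling the sample to 6000 per arm per round halves the within-PHC variance, from 3.016 to 1.508 squared points. At tau = 1 the rate becomes 2 × [1 - Phi(1.96 × sqrt(1.508/3.508))] = 2 × [1 - Phi(1.285)], about 20%, up from 13%. More respondents narrow the reported interval around a quantity that still contains the PHC's own drift.

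**The case against.** The strongest reply is that the plan uses difference in differences, so fixed differences between PHCs cancel. That stands. A reader might infer that the effect cannot be separated from any difference between PHCs; the documents do not support that, and only PHC-specific change is aliased. All four PHCs lie in one block, which makes shared trends plausible and tau perhaps small. That is fair, but it does not establish a small tau, and one PHC per arm leaves no way to estimate it. At 0.25 to 0.5 points the inflation is slight.

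Three other stronger readings should be resisted.

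- That no randomisation-based test exists. One does, with a floor of 1/6 under the four-arm sharp null; it simply cannot reach 0.05.
- That the planned Z-test would give false-positive rates of 28% (tau = 1) and 47% (tau = 2). These follow if its standard error ignores within-PHC clustering (1.23 points instead of 1.74), but the rate is then already 16.6% at tau = 0. That part is a separate defect, and the article does not describe the variance to be used.
- That feasibility falls with efficacy. It does not. Table 3 lists feasibility as a primary indicator, and delivery measures can be described within each arm without replication between PHCs.

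Activity under the national NCD programme is also a weak example of local drift, because the rationale section says that ages 10-30 are not covered by it.

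A statistical analysis plan not shown here could improve the standard errors. It could not create a second PHC per arm. Treating villages as clusters would capture village variation only, since villages were not randomised and all those in an arm share one PHC.

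**Conclusion.** The point holds in this form: PHC-specific change between surveys is completely aliased with each intervention and has no error term. This is structural and rests on no assumed value. The aim of demonstrating the efficacy of each modality, and the statement about a very large sample, therefore claim a property that the design lacks.

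The size of the inflation does rest on assumption. Under the conditions in the working it runs from 5% at tau = 0 to 31% at tau = 2 points. At tau = 2 the SD of the difference in change between two PHCs is 2 × sqrt(2) = 2.8 points, close to the whole 3.25-point target. The text should be corrected before results are reported.

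**What to change.** 1. Study Design: describe the study as a four-area controlled before-and-after comparison with areas allocated by lottery.
2. Statistical Analysis Plan: keep feasibility for each modality. Replace the efficacy aim with estimating the change in each intervention PHC relative to the control PHC, conditional on these four PHCs.
3. Strengths and Limitations: delete the claim that sample size minimises random error, and list one PHC per arm as the main limitation.
4. Optional: report with each estimate D the tau at which its 95% interval would include zero, tau* = sqrt([(|D|/1.96)² - SE²] / 2), with SE the within-PHC standard error. If |D| is below 1.96 × SE, the interval includes zero even at tau = 0.

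The cost is rewording, one short calculation if item 4 is taken up, and a weaker stated conclusion. No extra participants or field work are needed. Randomising villages or adding PHCs per arm would give real replication. The study was to start in January 2022 and the article appeared in September 2023, so that is probably no longer open, and this fix does not depend on it.
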